### Part 3: Impact of Oral diseases on Adolescents daily performance

32. During the past three months how often the problems with your mouth and teeth caused you any difficulty with eating or enjoying food?

1. Never
2. Once or twice a month
3. Once or twice a week
4. Every or nearly everyday

|  |
|--|
|  |
|  |
|  |
|  |

33. During the past three months how often the problems with your mouth and teeth caused you any difficulty with speaking or pronouncing words?

1. Never
2. Once or twice a month
3. Once or twice a week
4. Every or nearly everyday

|  |
|--|
|  |
|  |
|  |
|  |

34. During the past three months how often the problems with your mouth and teeth caused you any difficulty with cleaning teeth?

1. Never
2. Once or twice a month
3. Once or twice a week
4. Every or nearly everyday

|  |
|--|
|  |
|  |
|  |
|  |

35. During the past three months how often the problems with your mouth and teeth caused you any difficulty with sleeping and relaxing?

1. Never
2. Once or twice a month
3. Once or twice a week
4. Every or nearly everyday

|  |
|--|
|  |
|  |
|  |
|  |

36. During the past three months how often the problems with your mouth and teeth caused you any difficulty with smiling, laughing, showing teeth without embarrassment?

1. Never
2. Once or twice a month
3. Once or twice a week
4. Every or nearly everyday

|  |
|--|
|  |
|  |
|  |
|  |

37. During the past three months how often the problems with your mouth and teeth caused you any difficulty in maintaining usual emotional state without being irritable?

1. Never
2. Once or twice a month
3. Once or twice a week
4. Every or nearly everyday

|  |
|--|
|  |
|  |
|  |
|  |

38. During the past three months how often the problems with your mouth and teeth caused you any difficulty with carrying out school activities such as attending class or social role?

1. Never
2. Once or twice a month
3. Once or twice a week
4. Every or nearly everyday

|  |
|--|
|  |
|  |
|  |
|  |

39. During the past three months how often the problems with your mouth and teeth caused you any difficulty with enjoying contact with people?

1. Never
2. Once or twice a month
3. Once or twice a week
4. Every or nearly everyday

|  |
|--|
|  |
|  |
|  |
|  |

**THANK YOU**

Appendix 2: Clinical data collection form

**EFFECTIVENESS OF MODIFIED BASIC PACKAGE OF ORAL CARE ON ORAL HEALTH STATUS AND RELATED QUALITY OF LIFE AMONG ZAMBIAN ADOLESCENTS:-A FIELD TRIAL**

|                   |                                                                                     |                                                 |                                                 |                     |                                                                 |             |                                                 |                                                 |                                                 |
|-------------------|-------------------------------------------------------------------------------------|-------------------------------------------------|-------------------------------------------------|---------------------|-----------------------------------------------------------------|-------------|-------------------------------------------------|-------------------------------------------------|-------------------------------------------------|
| Adolescent's Id   |     | Gender                                          |                             | (1) Boy
(2) Girl |                                                                 | Birth date? |  
DD |  
MM |  
YY |
| Examination date? |  
DD                                     |  
MM |  
YY | Data                | (1) Baseline
(2) follow up (circle)                          | Duplicate   |                             | (1) Original
(2) Duplicate                   | Examiner ID                                     |
|                   |                                                                                     |                                                 |                                                 |                     | 1 st 2 nd 3 rd 4 th |             |                                                 |                                                 |                                                 |

| Part 1 : Caries Assessment Spectrum and Treatment (CAST) record form |              |    |    |    |    |    |    |    |    |    |    |    |    |    |
|----------------------------------------------------------------------|--------------|----|----|----|----|----|----|----|----|----|----|----|----|----|
| Surface                                                              | Tooth Number |    |    |    |    |    |    |    |    |    |    |    |    |    |
|                                                                      | 17           | 16 | 15 | 14 | 13 | 12 | 11 | 21 | 22 | 23 | 24 | 25 | 26 | 27 |
| D                                                                    |              |    |    |    |    |    |    |    |    |    |    |    |    |    |
| O                                                                    |              |    |    |    |    |    |    |    |    |    |    |    |    |    |
| M                                                                    |              |    |    |    |    |    |    |    |    |    |    |    |    |    |
| B                                                                    |              |    |    |    |    |    |    |    |    |    |    |    |    |    |
| L                                                                    |              |    |    |    |    |    |    |    |    |    |    |    |    |    |
|                                                                      |              |    |    |    |    |    |    |    |    |    |    |    |    |    |
|                                                                      | 47           | 46 | 45 | 44 | 43 | 42 | 41 | 31 | 32 | 33 | 34 | 35 | 36 | 37 |
| D                                                                    |              |    |    |    |    |    |    |    |    |    |    |    |    |    |
| O                                                                    |              |    |    |    |    |    |    |    |    |    |    |    |    |    |
| M                                                                    |              |    |    |    |    |    |    |    |    |    |    |    |    |    |
| B                                                                    |              |    |    |    |    |    |    |    |    |    |    |    |    |    |
| L                                                                    |              |    |    |    |    |    |    |    |    |    |    |    |    |    |

**art 1 key CAST Codes**

| Characteristic      | Code | Description                                                                                                                                                          |
|---------------------|------|----------------------------------------------------------------------------------------------------------------------------------------------------------------------|
| Sound               | 0    | No visible evidence of a distinct carious lesion is present                                                                                                          |
| Sealant             | 1    | Pits and/ or fissure are at least partially covered with a sealant material                                                                                          |
| Restoration         | 2    | A cavity is restored with an (in)direct restorative material                                                                                                         |
| Enamel              | 3    | Distinct visual change in enamel only; a clear caries-related discolouration is visible, with or without localised enamel breakdown                                  |
| Dentine             | 4    | Internal caries-related discolouration in dentine; the discoloured dentine is visible through the enamel, which may or may not exhibit a visible localised breakdown |
|                     | 5    | Distinct cavitation into dentine; the pulp chamber is intact                                                                                                         |
| Pulp                | 6    | Involvement of the pulp chamber; distinct cavitation reaching the pulp chamber, or only root fragments are present                                                   |
| Abscess/
fistula | 7    | A pus-containing swelling or a pus-releasing sinus tract related to a tooth with pulpal involvement                                                                  |
| Lost                | 8    | The tooth has been removed because of dental caries                                                                                                                  |
| Other               | 9    | Does not match with any of the other descriptions                                                                                                                    |

Adolescents Id No.....

| Part 2 : Plaque Index by Silness & Loe |             |    |    |
|----------------------------------------|-------------|----|----|
|                                        | Index teeth |    |    |
| Surface                                | 16          | 11 | 26 |
| Buccal                                 |             |    |    |
| Lingual                                |             |    |    |
|                                        | 46          | 41 | 36 |
| Buccal                                 |             |    |    |
| Lingual                                |             |    |    |

#### Key for part 2

B=Buccal, L=Lingual, M=Mesial, D= Distal , PI=Plaque Index (Total score for B,L, M and D divide by 4)

Codes

|   |                                                              |
|---|--------------------------------------------------------------|
| 0 | Plaque not visible nor cannot be wiped off with the explorer |
| 1 | Plaque not visible but can be wiped off with the explorer    |
| 2 | Plaque is visible along the gingival no need to probe        |
| 3 | Thick plaque is visible along gingival margin                |

#### Notes

- If the index tooth is missing score the nearest tooth in that sextant
- If there is no tooth in that sextant indicate X
- The overall score is sum of the 12 surfaces scores (maximum of 36)

Adolescents Id No.....

| Part 3: Gingival bleeding scores according to Silness-Löe plaque index |             |    |    |
|------------------------------------------------------------------------|-------------|----|----|
|                                                                        | Index teeth |    |    |
| Surface                                                                | 16          | 11 | 26 |
| Buccal                                                                 |             |    |    |
| Lingual                                                                |             |    |    |
|                                                                        | 46          | 41 | 36 |
| Buccal                                                                 |             |    |    |
| Lingual                                                                |             |    |    |

**Codes** 0= No inflammation (Normal gingival, no discoloration, no bleeding)

1= Mild inflammation (slight color change, mild alteration of gingival surface, no bleeding)

2= Moderate inflammation (erythema, swelling, bleeding on probing or when pressure is applied)

3= Severe inflammation (severe erythema and swelling and tendency towards spontaneous bleeding, some ulceration)

## Appendix 6- Analysis Plan by objectives

| No | Objective                                                                                                                                                                       | Analysis                                                                   | To be reported as                                              |
|----|---------------------------------------------------------------------------------------------------------------------------------------------------------------------------------|----------------------------------------------------------------------------|----------------------------------------------------------------|
| 1  | To determine prevalence and distribution of dental caries, periodontal conditions and oral impacts on daily performance among adolescents in Copperbelt Province, Zambia        | Frequency distribution, chi-square test, logistic regression               | Number and percentage, odds ratio with 95% confidence interval |
| 2  | To determine the association between dental caries and oral health related quality of life among adolescents in Copperbelt Province                                             | Frequency distribution, chi-square test, hierarchical logistic regression  | Number and percentage, odds ratio with 95% confidence interval |
| 3  | To assess the effects of a six months modified basic package of oral care intervention on knowledge and behaviors related to dental caries after 18 and 24 months of follow up. | Frequency distribution, chi-square test, generalized estimating estimation | Number and percentage, odds ratio with 95% confidence interval |
| 4  | To assess the effects of a six months modified basic package of oral care intervention on prevalence of dental caries after 6 and 12 months of follow up                        | Frequency distribution, chi-square test, generalized estimating estimation | Number and percentage, odds ratio with 95% confidence interval |
| 5  | To assess the effects of a six months modified basic package of oral care intervention on prevalence of oral impacts on daily performance after 18 and 24 months of follow up   | Frequency distribution, chi-square test, generalized estimating estimation | Number and percentage, odds ratio with 95% confidence interval |

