### **2.2. Specific Objectives**

- 1 To determine prevalence and distribution of dental caries, periodontal conditions and oral impacts on daily performance among adolescents in Copperbelt Province, Zambia
- 2 To determine the association between dental caries and oral health related quality of life among adolescents in Copperbelt Province
- 3 To assess the effects of a six months modified basic package of oral care intervention on knowledge and behaviors related to dental caries after 18 and 24 months of follow up.
- 4 To assess the effects of a six months modified basic package of oral care intervention on prevalence of dental caries after 18 and 24 months of follow up
- 5 To assess the effects of a six months modified basic package of oral care intervention on prevalence of oral impacts on daily performance after 18 and 24 months of follow up

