## **4.9. Data collection procedures**

### **4.9.1. Data collection tools and indices**

Data will be collected using self-administered structured questionnaire and oral clinical examination. The questionnaire (Appendix 1) will be in English and will inquire on; demographic information of the participant's oral health knowledge and related behaviors and impact of oral diseases on daily performance of the adolescent. It will further inquire on parental/guardian socio-economic status using international wealth index (Smits and Steendijk, 2015). The students will understand the questions for the reason that they are fluent in English language.

Oral clinical examination will be done in a well illuminated classroom by two trained and calibrated dentists. Examination will be done using dental explorer aided by a mouth mirror and artificial light. The participants' will be lying on a desk and the examiner seated behind the participant's head. Every examiner will have one recorder who will be seated close to the examiner to ensure that the findings are recorded correctly.

Data collection will be done in four phases; baseline, every six months after institution of intervention that is; first follow up (6 months), second follow up (12 months), third follow up (18 months) and last follow up (24 months). The data collected for every adolescent will be paired and analyzed in pair. The principal investigator will assign a range of numbers for each school to be used as adolescent's identity number for baseline and all follow ups. School teachers will then be requested to create a list of names according to attendance register of that school and assign numbers to the individual participants. A copy of list of names and ID numbers will be kept by head teacher in case the teacher responsible for health is absent. Data for each variable will be entered and analyzed as set (baseline, 1st, 2nd, 3rd and 4th follow up).

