#### **4.10. Study outcomes**

The expected primary outcomes are improved oral health (dental caries status and gingivitis) and OHRQoL. The secondary outcomes include improved oral hygiene (plaque score) and oral health knowledge and related behaviors. The effect sizes for improvement in oral health and oral health related quality of life are based on average improvement achieved in similar studies reviewed.

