#### **4.12. Data entry cleaning and analysis**

Data entry, coding and processing will be done using a computer software program IBM SPSS for Windows (Version 23). Frequency distribution for proportions, means (SD), cross tabulation with chi –square and binary logistic regression reported in odds ratio and 95% (CI) will be performed per respective objectives.

Frequency distribution for proportions of adolescents with plaque, gingival bleeding, poor oral health behaviors and oral health related quality of life. Dental caries experience will be summarized as number and percentage. Furthermore, cross tabulation for bivariate comparison of differences in intervention outcome variables by socio-demographics, study arms and oral health behaviors will be conducted. To examine for the differences between the groups (effectiveness of trial intervention) generalized estimating equations will be performed and reported in odds ratio and 95% confidence interval. A statistical significance difference shall be assumed when  $p \leq 0.05$ . Analysis plan per objective is summarized in appendix 6.

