#### **4.14. Study limitation and mitigation**

##### **Study limitations**

1. The follow up duration will be limited to 24 months which is enough to observe change in oral health related behaviors, plaque and bleeding but not reasonably enough for observing dental caries increment.
2. The study will follow single blind design where only the examiners will be blinded, the principal investigator and the participants will not be blinded due to the nature of the intervention which requires administration of educational technical materials and provision of treatment which cannot be easily concealed.
3. Adolescents may modify their oral health related behavior in response to awareness that there are being observed (Hawthorne effects).

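### Caries, a primary outcome, is assessed at 18 and 24 months in objective 4 but at 6 and 12 months in its row of the analysis plan

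*Protocol*

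**What the plan says.** Section 2.2, objective 4, concerns the effect of the intervention on "prevalence of dental caries after 18 and 24 months of follow up". Section 4.12 then directs the reader to a table: "Analysis plan per objective is summarized in appendix 6". In that table, row 4 carries the same objective number and otherwise the same wording, but reads "prevalence of dental caries after 6 and 12 months of follow up".

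The neighbouring rows agree with section 2.2. Row 3 covers "knowledge and behaviors related to dental caries after 18 and 24 months of follow up", and row 5 covers "prevalence of oral impacts on daily performance after 18 and 24 months of follow up".

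Section 4.10 gives the standing of the outcome: "The expected primary outcomes are improved oral health (dental caries status and gingivitis) and OHRQoL". Section 4.9.1 schedules follow-up data collection at 6, 12, 18 and 24 months. On the length of follow-up, the first limitation in section 4.14 says that 24 months suffices for behaviours, plaque and bleeding, "but not reasonably enough for observing dental caries increment".

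**The concern.** The protocol fixes the analysis times for a primary outcome twice and gives different answers. An analyst who follows Appendix 6 as written would test caries at two visits that objective 4 does not name, and would find no row for the two visits that it does name.

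Because all four examinations take place, nothing in the conduct of the trial forces the question into the open. The caries result could be reported at either pair of visits, each with a passage to cite, and the choice could be made after the data are seen. The principal investigator and participants are unblinded (section 4.9.2). The blinding of the data analyst promised in section 4.14 is aimed at missing data, transformations, subgroups and covariates. It does not determine which visits answer the objective.

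**Working it through.** This is a comparison of texts. The only relevant arithmetic is a check on whether the sample size settles the matter.

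**1. Times for the three effect objectives**

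| Objective | Section 2.2 | Appendix 6 | Agree? |
|---|---|---|---|
| 3, knowledge and behaviours | 18 and 24 months | 18 and 24 months | yes |
| 4, caries prevalence | 18 and 24 months | 6 and 12 months | **no** |
| 5, oral impacts | 18 and 24 months | 18 and 24 months | yes |

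Neither version of objective 4 is marked as superseded, and both stand in current text.

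**2. Does the visit schedule settle it?** No. Section 4.9.1 includes all of 6, 12, 18 and 24 months, so both versions are feasible.

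**3. Does the sample size settle it?** Section 4.4 gives:

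- 2N = 4 × (1.96 + 1.03)² × 1.34² / 0.268² = 4 × 8.9401 × 25 = 894.01, taken as 894
- design effect = 1 + (80 − 1) × 0.01 = 1.79, and 894 × 1.79 = 1600.26, taken as 1600
- allowance for loss to follow-up: 1600 × 1.10 = 1760

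All three stated figures reproduce. The formula concerns a difference in mean DMFT and contains no time point, so it favours neither version.

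**4. What does the protocol say about early and late visits?** Section 4.14 bears on this in two places.

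- The limitation on caries is stated for 24 months. Visits at 6 and 12 months give less follow-up still, and so do less well by the protocol's own criterion.
- The mitigation of Hawthorne effects depends on the last follow-up, placed six months after the intervention ends. Row 4 excludes that visit for caries, whereas objective 4 includes it.

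**5. A related inconsistency.** Objectives 3 to 5, in section 2.2 and in Appendix 6, describe a six-month intervention. Section 4.6 describes toothpaste and peer education for 18 months, and the mitigation in section 4.14 (24 − 6 = 18) fits the latter. Where the 6- and 12-month visits fall relative to the end of the intervention therefore depends on which passage is read.

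**The case against.** The strongest reply is that this is a copying slip with little consequence. Rows 3 and 5 match section 2.2, and row 4 keeps the objective's number and remaining wording. Its method and reporting columns do not depend on the visit. Section 4.12 calls Appendix 6 a summary, and section 4.9.1 says that each variable is analysed as a set covering baseline and all four follow-ups, so caries at 18 and 24 months would be analysed anyway. Much of this stands. A slip is the likeliest explanation, although the protocol does not say so, and it would be too strong to claim that the later caries data would go unanalysed. But analysing every visit does not say which visits answer objective 4, and on that the two passages still disagree.

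A reader might go further and infer that almost no preventable caries can have accrued by 6 or 12 months, so that a test then is nearly bound to be null. The documents do not support this:

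- The protocol gives no caries incidence. Its literature review cites toothbrushing interventions with follow-up from 6 months to 3 years and reductions of 24-50% in the proportion with caries.
- CAST code 3 records enamel lesions, and section 4.14 chose CAST in order to capture early stages.
- The package is curative as well as preventive. Table 1 puts the first ART and OUT sessions in months 1-2, and a filled cavity moves to CAST code 2. Objective 4 does not say whether a restored surface still counts towards prevalence; if it does not, the arms could differ by 6 months.

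Nor can power at the earlier visits be obtained by scaling the section 4.4 formula. That formula is undated and concerns mean DMFT, whereas objective 4 concerns a prevalence, analysed by generalized estimating equations and reported as an odds ratio. Scaling would also need an assumed pattern of accrual.

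Finally, a reader might conclude that no effectiveness test should be allowed at 6 or 12 months. Nothing in the protocol requires that. It is enough to make the standing of such comparisons clear.

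**Conclusion.** The contradiction is real and needs correcting. For a declared primary outcome, the protocol supports two non-overlapping pairs of analysis times: 18 and 24 months in the objective, and 6 and 12 months in the analysis plan. This goes beyond a clerical blemish, because following the table as written would test the outcome at visits that its objective does not name.

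The extent is one row of one table. The sample size, visits and data collection are unaffected, and no loss of power can be quantified from what the protocol gives. The finding rests on the wording of the two passages and needs no assumption about caries incidence. That the row 4 times are the less suitable pair rests only on section 4.14: shorter follow-up than the 24 months already called inadequate for increment, and omission of the 24-month visit.

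**What to change.** In Appendix 6, row 4, replace 6 and 12 months by 18 and 24 months, so that it agrees with objective 4 and with rows 3 and 5. Do this before outcome data are analysed. Add a sentence stating that any caries comparisons at 6 and 12 months are secondary to those at 18 and 24 months. Should the sponsor really have intended the earlier visits, section 2.2 would have to change instead, with a reason. Either way the two passages must agree.

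The cost is one table entry and one sentence, with no change to the sample size of 1760, the visits or the data collected.

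Separately, the six-month intervention named in the objectives and the 18 months described in section 4.6 must be reconciled, since the meaning of every follow-up time depends on when the intervention ends.
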